### Assessment of harms

Trained research assistants will screen all potential participants and exclude those with health-related problems that might hinder participation or be worsened by yoga. Throughout the study, all adverse events will be reported, evaluated and followed up by a research assistant. Any adverse events needing medical attention will be addressed and referred to appropriate medical professionals. Adverse events will be formally assessed at 6-week follow-up and at post intervention (12+1 weeks) by asking participants if they had experienced any worsening of symptoms, injuries or other adverse efforts during the trial. Participants who report adverse events will be advised to see their general practitioner for further evaluation. All participants will be instructed to contact the study coordinator if any adverse events occur during the intervention. Decisions of participant or study discontinuation based on adverse effects will be made by the principal investigator. Participants can decide to dropout from the study at any given time. The yoga instructors are certified by the Yoga Alliance Guidelines and trained in minimising the risk of injuries and harm.

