#### Measures to maintain adherence

The yoga studio chosen for the intervention is located close to public transport connections. A research assistant will contact each yoga participant by phone every 2 weeks to discuss any adherence-related issues (eg, transport or motivation). Participants will be encouraged to contact the study research assistant if they experience an adverse event, such as pain or injury, related to yoga. A research assistant will conduct a 6-week mid-intervention follow-up (all participants) to assess adherence and adverse events. Yoga participants will complete a weekly exercise diary and attendance will be recorded at the yoga studio.

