
### Sample size

As there are no published RCTs of yoga for post COVID, the power estimate was based on data from our RCT of yoga-based exercise for well-being among physically inactive older adults,^41^ conducted in the same setting. A sample size of 35 participants per condition (yoga and health promotion intervention) would provide ~90% power (two-tailed α=0.05) to detect an effect size of 0.28 (small) on the primary outcome (SF-36). This equates to a postintervention group difference of ≥5 points (or ≥0.5 SD increase/improvement) on each of the two summary scores (mental and physical components). With an expected dropout rate of 20% and 1:1 allocation, the total number of participants estimated at baseline is 88.

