There are some unique challenges associated with this trial. Given that fatigue is a common symptom among patients with post COVID, some participants may find it challenging to complete the intervention, potentially leading to higher than predicted attrition rates. To reduce the risk of attrition bias, fortnightly phone calls to the yoga participants will be conducted, during which adherence and motivational issues will be discussed with a research assistant trained in cognitive psychology. Offering yoga memberships to participants in the health promotion group (following completion of the trial) serves as an incentive to complete the trial. Another potential challenge is the scheduling of classes to avoid conflicts with work or other commitments. To overcome this, classes will be offered at various times on weekdays, with the option to attend online on occasions when it is inconvenient to travel to the studio. However, participants will be encouraged to join onsite classes to gain the most benefit from the programme, especially during the first few weeks of the trial. A potential limitation is that the study lacks long-term follow-up, and thus, maintenance of intervention effects cannot be examined. Findings from the trial will be used to support grant applications for studies involving long-term assessments (12 months) and mechanistic effects of yoga in post COVID.

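### Adverse events are actively asked about only at week 6 and week 12+1, with no question stated at withdrawal, so harms among leavers may be under-counted

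*Protocol article*

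**What the plan says.** The protocol article's Assessment of harms section sets two scheduled occasions: "Adverse events will be formally assessed at 6-week follow-up and at post intervention (12+1 weeks"). The question is put "by asking participants if they had experienced any worsening of symptoms, injuries or other adverse efforts during the trial", so symptom worsening counts, not only injury.

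The same section adds a continuous route. It states that "Throughout the study, all adverse events will be reported, evaluated and followed up by a research assistant" and that "All participants will be instructed to contact the study coordinator if any adverse events occur during the intervention". It gives the principal investigator the decision on discontinuation because of adverse effects, and it lets participants leave at any time. Randomisation and blinding names an adverse event that brings participation to an end as a ground for unblinding.

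Measures to maintain adherence describes phone calls every 2 weeks to yoga participants, "to discuss any adherence-related issues (eg, transport or motivation"). Yoga participants are also encouraged to get in touch "if they experience an adverse event, such as pain or injury, related to yoga", and they keep a weekly exercise diary. No equivalent calls or diary are described for the health promotion arm, which receives fortnightly emailed links.

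On attrition, Sample size assumes dropout: "With an expected dropout rate of 20% and 1:1 allocation", 88 are to be randomised. The Discussion notes that, because of fatigue, "some participants may find it challenging to complete the intervention, potentially leading to higher than predicted attrition rates", and answers this with the fortnightly calls.

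**The concern.** An event that is asked about is recorded more reliably than one the participant must volunteer. Here the asking is tied to two visits, and people who withdraw are those least likely to attend them. No section states an adverse-event question at withdrawal or in the fortnightly calls. A participant who feels worse, stops coming and withdraws in the first weeks can leave without ever being asked.

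The between-visit prompt given to yoga participants is also narrower than the formal question. Its examples are pain and injury, and it is limited to events related to yoga. Someone with a flare of fatigue may not think it fits.

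This matters because worsening of symptoms is a central safety question for an activity programme in this population. The Introduction says that common symptoms may hinder aerobic exercise and strength training or be made worse by them. The Discussion foresees referral of patients with mild-to-moderate symptoms to yoga practitioners. If leaving is related to worsening, a harm count that depends on staying will be too low, and the analysis cannot recover answers that were never sought. Multiple imputation of the efficacy outcomes does not touch this.

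**Working it through.** **Expected number of leavers (from the plan)**

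- Inputs from Sample size: 35 evaluable per arm, 20% dropout, 88 randomised 1:1.
- Per arm: 35 / (1 − 0.20) = 43.75, rounded up to 44.
- Total: 70 / (1 − 0.20) = 87.5, rounded up to 88. The plan's figure is reproduced.
- Leavers: 44 − 35 = 9 per arm, 18 in total.

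**What each group is asked**

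| Participant | Week 6 question | Week 12+1 question | Other routes stated |
|---|---|---|---|
| Stays in the study | yes | yes | own contact with the coordinator; calls and diary (yoga only) |
| Stops classes but stays in the study | yes | yes | as above |
| Withdraws after week 6 | yes | no | own contact; investigator-led discontinuation if the event is recognised |
| Withdraws before week 6 | no | no | as above |

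The 20% covers the whole trial. The article does not split it at week 6, so the number in the last row is unknown.

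**Illustration of size, yoga arm (event rates are assumptions; the article gives none)**

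Recorded participants with an event = (stayer rate × 35) + (leaver rate × 9 × share of leavers' events captured), over 44 randomised.

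With a stayer rate of 10% and a leaver rate of 50%:

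- Stayers: 0.10 × 35 = 3.5. Leavers: 0.50 × 9 = 4.5.
- None captured: 3.5 / 44 = 8.0%.
- Half captured: (3.5 + 2.25) / 44 = 5.75 / 44 = 13.1%.
- All captured: (3.5 + 4.5) / 44 = 8.0 / 44 = 18.2%.

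Range over the leaver rate, with stayers at 10% and full capture:

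- 30%: 3.5 + 2.7 = 6.2, or 6.2 / 44 = 14.1%.
- 80%: 3.5 + 7.2 = 10.7, or 10.7 / 44 = 24.3%.

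The no-capture figure stays at 3.5 / 44 = 8.0% throughout. It applies only if every leaver's event goes unasked and unreported.

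**The case against.** The strongest reply is that the article already provides for this. Reporting is continuous and covers both arms, all participants are told to contact the coordinator, and both discontinuation for adverse effects and unblinding on such grounds are foreseen. Leaving because of harm is thus a recognised category. All participants are due in person at 6 weeks and the analysis is by intention to treat, so someone who merely stops attending classes should still be asked. Data management refers to standard operating procedures, and a withdrawal form may exist there. All of this stands. It turns a claim of certain loss into one of risk. It does not remove the risk, because the discontinuation and unblinding provisions act only once an event has been recognised, and the only stated between-visit route to recognition is that the participant speaks up.

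Three stronger readings are tempting and are not supported:

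- **That those who leave because they got worse are the ones missing from the harm count, logged only as non-adherent.** No section says how such a withdrawal is coded, and the continuous route can capture it.
- **That the adherence section and the Discussion contradict the harms section.** The Discussion speaks of fatigue as a common symptom of the condition that may make completion hard. That is not the same as worsening after yoga. Transport and motivation are only examples of what the calls may cover.
- **That the plan would report 10% where the truth is 18%.** The 10% is 3.5/35, and the article nowhere says that harms will be reported over completers only. The event rates are assumed, and total failure of spontaneous reporting is the worst case.

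The extra contact in the yoga arm also cuts the other way. Calls and diaries give yoga participants more chances to mention an event, which could raise the yoga count relative to control. The net direction of bias in the between-arm comparison is therefore not determined.

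**Conclusion.** The point holds as a weakness in how harms are ascertained. Solicited questioning is fixed at two visits, none is stated at withdrawal, and unscheduled events depend mainly on participants volunteering them, with unequal contact between arms. About 9 people per arm are expected to miss at least the final question, and an unknown number of these to miss both.

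Under the assumed rates, the recorded yoga-arm figure lies between 8% and 18% depending on how much of the leavers' harm is captured, with 13% at half capture. These figures show how much could turn on capture among leavers; they do not predict the trial's result. They rest on the plan's 20% dropout applying to the yoga arm and on leavers having more events than stayers. The Discussion makes fatigue-related attrition plausible but does not establish that higher rate.

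**What to change.** Amend Assessment of harms to state that:

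1. the existing adverse-event question, together with the reason for leaving, is asked in both arms at the last contact with anyone who withdraws or misses the 6-week or 12+1-week visit, by phone or REDCap form if needed;
2. a withdrawal attributed to worse symptoms is recorded as an adverse event in either arm;
3. harms are reported over all randomised participants, with the number never asked shown per arm.

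Missed classes should not be entered as adverse events. Only the yoga arm has classes, so this would make ascertainment one-sided.

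If a withdrawal form covering items 1 and 2 already exists in the operating procedures, one sentence confirming it would do for those items. If data collection is complete, item 3 can still be applied.

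The cost is one short form. Some leavers will decline to answer, which is why the number never asked or not answering should be visible in the report.

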### Patient and public involvement

During the development of this trial, we contacted the Swedish COVID-19 Association and the largest COVID-19 treatment clinic to obtain their views regarding the inclusion and exclusion criteria proposed in our study design. Based on their feedback, some minor changes to these criteria were made. With the exception of this important element of the study, we did not directly involve the public in other aspects of the study design. The research questions and measures included in the trial were chosen by a multidisciplinary team of researchers that includes specialist physicians involved in the treatment of post COVID patients.

### Ethics and dissemination

The trial is approved by the Swedish Ethical Review Authority (Etikprövningsmyndigheten), number 2023/06518-01. All participants will be informed about the aims and procedure of the study prior to participation. Written informed consent will be obtained by a research assistant prior to enrolment in the study from all participants (see consent form in online supplemental file 3) Confidentiality, voluntariness and freedom to withdraw participation at any time will be stated. Participants will give written informed consent to include their non-identified data in aggregate analyses that will be published in a scientific journal. No identifying or personal details of participants will be presented in any form. The findings of the study will be published in leading scientific journals and presented at conferences and seminars to key stakeholders. We have plans to disseminate the findings back to the Swedish COVID Association and a selection of COVID-19 clinics and health centres. A summary of key results will be published for participants of the study and the general population through newspaper articles, press releases and media channels.

## Discussion

Post COVID remains prevalent, yet there is no agreed treatment regime due to the heterogenous profile of the condition; consequently, many clinicians struggle to provide effective treatments. This RCT aims to broaden the array of potentially effective treatment options by examining the effects on HR-QoL of a yoga-based intervention, designed specifically for adults diagnosed with post COVID. The findings will provide new insights into the effects of a lifestyle-based intervention that can be self-maintained beyond the 12-week programme. The intervention is likely to improve the health and well-being of those with post COVID symptoms and has the potential to be incorporated into clinical practice (eg, by referring those with mild-to-moderate symptoms to appropriately trained yoga practitioners). Further, it may encourage research on lifestyle treatments for related chronic conditions, or research on yoga’s effect on physiological mechanisms (eg, why pulmonary function may be enhanced by yoga, how yoga practice affects inflammatory biomarkers, how metabolism is affected, etc). Trials have been conducted using specific components of yoga in post COVID context, such as breathing techniques,^44^ meditation techniques for cognition^45^ or online-based yoga for psychological well-being.^46^ This is the first RCT to investigate the effects of a complete yoga programme specifically designed for adults with post COVID on HR-QoL and secondary health outcomes.

Post COVID can be difficult to diagnose, being dynamic and multisymptomatic, and an individualised treatment plan may take time to initiate. Symptomatic treatment varies on a patient-to-patient basis and may include pharmacotherapy or rehabilitation.^47^ Most medical treatments provide only partial symptom relief, and many have side effects, resulting in poor compliance. Rehabilitative treatments include cognitive behavioural therapy for mental health and fatigue,^48 49^ physical therapy for pain^50^ and pulmonary rehabilitation.^51^ A comprehensive approach to a patient’s recovery often involves several treatments.

Yoga is a holistic treatment option for reducing allostatic load in post COVID.^23^ Yoga practice is discussed to have anti-inflammatory effects,^52^ and a proposed mechanism behind this may be enhanced melatonin production.^53^ Recent studies indicate that yoga may have a beneficial effect on the diversity and composition of the gut microbiome, which may reduce fatigue and improve immunity and mental health.^54^ Further, practicing yoga has been associated with positive effects on blood circulation and brain health.^55 56^ By stimulating the parasympathetic nervous system and the vagus nerve, yoga practice regulates the hypothalamic–pituitary–adrenal axis and improves heart rate variability,^10 57 58^ which is shown to be an indicator of cardiovascular and general health. Additionally, isometric poses have been associated with a reduction in fatigue and increased vitality in chronic fatigue syndrome, a condition sharing features with post COVID.^14^ Few treatment options offer integrated health benefits to the same extent as yoga practice.

Yoga-based exercise is a non-stigmatising, readily available and relatively inexpensive option, which could complement traditional medical care, potentially reducing the need for medication while improving HR-QoL. Yoga can be practised almost anywhere, guided by instructors onsite or digitally, and adjusted to meet the individual’s needs. Our recent collaborations with researchers in India have shown that yoga is a safe and feasible activity for adults with no previous experience^41 59 60^ and associated with fewer adverse events than moderate-intensity aerobic exercise.^61^

There are some unique challenges associated with this trial. Given that fatigue is a common symptom among patients with post COVID, some participants may find it challenging to complete the intervention, potentially leading to higher than predicted attrition rates. To reduce the risk of attrition bias, fortnightly phone calls to the yoga participants will be conducted, during which adherence and motivational issues will be discussed with a research assistant trained in cognitive psychology. Offering yoga memberships to participants in the health promotion group (following completion of the trial) serves as an incentive to complete the trial. Another potential challenge is the scheduling of classes to avoid conflicts with work or other commitments. To overcome this, classes will be offered at various times on weekdays, with the option to attend online on occasions when it is inconvenient to travel to the studio. However, participants will be encouraged to join onsite classes to gain the most benefit from the programme, especially during the first few weeks of the trial. A potential limitation is that the study lacks long-term follow-up, and thus, maintenance of intervention effects cannot be examined. Findings from the trial will be used to support grant applications for studies involving long-term assessments (12 months) and mechanistic effects of yoga in post COVID.

### Trial status

Protocol version 3 of 2024-08-14. Recruitment is planned to begin in the end of January 2024 with a total of three recruitment periods planned (spring 2024, fall 2024 and spring 2025). Data collection is estimated to be completed in May 2025.
